#### Control intervention

The participants in the control condition will receive treatment as usual (TAU), as this provides a fair comparison with routine clinical practice and will answer the question of whether JCP use is superior to current standard care. TAU includes, as a part of the Care Programme Approach (CPA), the need for service users to receive written copies of their care plan, including a prescriptive 'crisis contingency plan', in addition to regular contact with a care coordinator or allocated member of the clinical team. We anticipate that the CPA arrangements will be applied equally by routine services to intervention and control groups. Those participants allocated to receive a JCP will also continue to receive usual treatment from their CMHT in addition to creating a JCP. We do not anticipate that TAU will change during the course of the trial and will be documenting what TAU consists of through our collection of service use data.

### Assessments

#### Baseline assessments

(i) Socio-demographic details - age, sex, ethnicity, employment, educational, marital status

(ii) Details of self-harming behaviour over the preceding 6 months - measured using questions from Hawton et al [15]

(iii) Personality disorder status - Structured Clinical Interview for DSM-IV personality disorders (SCID-II) [16] - BPD subsection

(iv) Functional impairment - Work & Social Adjustment Schedule (WSAS) [17]

(v) Engagement with services - Service Engagement Scale [18]

(vi) Working Alliance - Working Alliance Inventory- Short Form (client version) (WAI-S) [19]

(vii) WAI-S (therapist version)

(viii) Health-related quality of life - Euroquol (EQ-5D) [20]

(ix) Satisfaction with care - Client Satisfaction Questionnaire (CSQ) [21]

(x) Perceived coercion - Treatment Experience Scale [22]

(xi) Service use - Adult Service Use Schedule (ADSUS) [23]

(xii) Alcohol use - Alcohol Use Disorders Identification Test (AUDIT) [13]

(xiii) Illicit substance use - Questionnaire on use of illicit substances taken over last year

(xiv) Emotional symptoms - Hospital Anxiety and Depression Scale (HADS) [14]

Additionally, socio-demographic data and length of practice data will be collected for care coordinators, using a proforma developed during the previous pilot work.

#### Follow-up assessments

Six months after randomisation, all participants will be followed-up. A research worker, blinded to treatment allocation, will arrange a convenient time to meet with the participant in order to complete the following measures:

i) Time to first act of self-harm (if any)

ii) Number of self-harm episodes over the preceding 6-month period

iii) Regarding the most recent act of self-harm - length of time from contemplation of self-harm to self-harm act

iv) Regarding the most recent act of self-harm - help-seeking behaviour prior to event (see 10.3)

v) WAI-S (client + therapist)

vi) WSAS

vii) Service Engagement Scale

viii) Treatment Experience Scale

ix) EQ-5D

x) CSQ

xi) ADSUS

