**Methods/Design:**

In this single blind exploratory randomized controlled trial, a total of 120 participants (age >18 years with a primary diagnosis of DSM-IV borderline personality disorder) will be recruited from community mental health teams and, after completing a baseline assessment, will be assigned to one of two conditions: (1) a Joint Crisis Plan, or (2) treatment as usual. Those allocated to the JCP condition will take part in a facilitated meeting, the purpose of which will be to agree the contents of the plan. Following the meeting, a typed version of the JCP will be sent to the patient and to any other individuals specified by the participant. All participants will be followed-up at 6 months. The primary outcome measures are: any self-harm event, time to first episode of self-harm and number of self-harm events over the follow-up period. Secondary outcome measures are length of time from contemplation to act of self-harm, help-seeking behaviour after self-harm, cost, working alliance, engagement with services and perceived coercion. Other outcome variables are quality of life, social impairment and satisfaction with treatment.

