### Eligibility criteria

#### Inclusion criteria

i) Age greater than or equal to 18 years

ii) Current contact with a Community Mental Health Team (CMHT)

iii) A primary diagnosis of DSM-IV Borderline Personality Disorder

iv) An episode of self-harm in the previous year

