### Self-harm follow-up data

Variables (i) and (ii) will be gathered from the following sources:

1. The follow-up interviews with participants at 6-months - participants will be asked to recall the approximate number of self-harm events occurring over the preceding six months. Variables (iii) and (iv) will be gathered using questions derived from Hawton et al [15].

2. Diaries: all participants will be supplied with a simple diary/calendar and will be asked to record all self-harm events on this (by simply circling the days of the month on which self-harm events occurred).

3. Electronic psychiatric case records.

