### Statistical analysis plan

An intention-to-treat analysis will be applied in the first instance (i.e. analysing all available data from randomised participants). The three data collection methods for the outcome of self-harm (i.e., participant interviews, diaries and electronic case records) are likely to differ on the amount of missing data. We will compare proportions of missing data using chi-square tests and agreement between data collection methods using Lin's Concordance Correlation Coefficient. Preliminary effectiveness estimates: Logistic regression will be used to compare proportions of patients that have self-harmed during the follow-up period in the two groups. Analysis of 'time to first self harm' outcome will also be conducted using survival analysis methods; log-rank test for bivariate comparisons and cox's proportional hazards to adjust for gender, stratification variables and time spent on treatment prior to randomisation. Other outcome assessments (continuous and binary) will be compared between the treatment groups at 6-month follow-up using t-tests, chi-square tests or non-parametric equivalents as appropriate, and regression modelling. The primary outcome analysis will be repeated on all three outcome collection methods to determine if conclusions remain the same. We expect little disparity in reporting of 'any self-harm episode' but potentially more in the time of first episode and number of episodes. If conclusions differ by the collection method used we will investigate reasons for the discrepancy. From this analysis we will be more certain of the appropriate collection methods for self-harm data and be better placed to decide on the appropriate outcome measure and estimate effectiveness in a future definitive trial.

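### Help-seeking is declared as behaviour after self-harm but listed for collection as behaviour before it, and both act-level secondary outcomes exist only for participants who self-harm, so testing them between arms is not a randomised comparison

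*Protocol article*

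**What the plan says.** The abstract (Methods/Design) lists among the secondary outcomes "length of time from contemplation to act of self-harm, help-seeking behaviour after self-harm".

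Under Follow-up assessments, two items correspond to these. Item (iii) is "Regarding the most recent act of self-harm - length of time from contemplation of self-harm to self-harm act". Item (iv) concerns the same act and is worded as "help-seeking behaviour prior to event (see 10.3"). The neighbouring items are worded differently. Item (i), time to first act, allows for there being none, and item (ii), the number of episodes, is limited to the preceding six months. Items (iii) and (iv) carry no time limit.

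The section Self-harm follow-up data says "Variables (iii) and (iv) will be gathered using questions derived from" a cited questionnaire, asked at the 6-month interview. It does not say whether the help-seeking questions concern the time before or after the act.

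Under Inclusion criteria, every participant must have had "An episode of self-harm in the previous year".

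The Statistical analysis plan section states that "Other outcome assessments (continuous and binary) will be compared between the treatment groups at 6-month follow-up". The methods it names are the usual two-sample tests, parametric or not, together with regression. The analysis uses all available data from randomised participants. The Power calculation section predicts 36% repeating self-harm under usual treatment (TAU) and 12% with the Joint Crisis Plan (JCP).

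**The concern.** There are two separate faults.

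The first is a contradiction about what the outcome is. Help sought before an act might avert it. Help sought afterwards is a response to it. A crisis plan could change one without the other. As written, one section declares the second and another collects the first, and no item in the follow-up list is named as help-seeking after the act. The service use schedule records contacts in general and is not described as tied to an act.

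The second is that both act-level outcomes depend on an event after randomisation that the intervention is meant to prevent. Someone who does not self-harm in follow-up has no contemplation-to-act time and no act around which to seek help. A test among those with data then compares people who self-harmed despite a JCP with people who self-harmed under usual treatment. Randomisation does not make those two groups alike.

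What is at stake is the reading of two secondary outcomes. The Discussion says the trial should inform the choice of candidate outcomes for a definitive trial, so an outcome with two meanings and a selected denominator could be carried forward.

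**Working it through.** **1. The wording side by side**

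| Place | Construct | Act referred to |
|---|---|---|
| Abstract, secondary outcomes | Help-seeking *after* self-harm | Not stated |
| Follow-up assessments (iv) | Help-seeking *prior to* the event | Most recent act |
| Self-harm follow-up data | Not stated; questions from a cited source | Not stated |

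The first two rows cannot both describe the same variable, and the third does not settle which is meant.

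**2. The plan's own sample size**

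Inputs from Power calculation: 36% v 12%, two-sided 5%, 80% power, 1:1.

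- Per arm, uncorrected: n = [1.960 × √(2 × 0.24 × 0.76) + 0.842 × √(0.36 × 0.64 + 0.12 × 0.88)]² / 0.24² = 48.5, rounded up to 49, a total of 98.
- With continuity correction: (48.5/4) × [1 + √(1 + 4/(48.5 × 0.24))]² = 56.5, rounded up to 57, a total of 114.

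The stated 114 is reproduced with the continuity correction, so 36% and 12% are the rates the plan rests on.

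**3. How many people can supply the two outcomes**

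With 120 randomised, 60 per arm:

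- TAU: 60 × 0.36 = 21.6
- JCP: 60 × 0.12 = 7.2
- Together: 28.8 of 120, or 24%

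This is before any loss to interview. The fraction with data differs threefold between arms.

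**4. What such a comparison could detect**

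Standardised difference detectable at 80% power, two-sided 5%:

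- Normal approximation, 21.6 v 7.2: (1.960 + 0.842) × √(1/21.6 + 1/7.2) = 2.802 × 0.430 = 1.21 SD.
- Noncentral t, 22 v 7: 1.26 SD.
- For comparison, 60 v 60: 2.802 × √(2/60) = 0.51 SD.

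For an assumed true difference of 0.5 SD, power is about 20% with 22 v 7, against about 78% with 60 v 60.

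**5. Why the comparison is selected**

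The documents give no help-seeking rates, so the values here are assumptions used only to show the mechanism. Suppose 12% would self-harm under either arm, a further 24% would self-harm under TAU but not with a JCP, and the JCP changes nobody's help-seeking. Among those with an act, the TAU rate is (0.12 × a + 0.24 × b)/0.36 and the JCP rate is a. Here a is the help-seeking probability in the first group and b that in the second.

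| a | b | TAU | JCP | JCP minus TAU |
|---|---|---|---|---|
| 0.30 | 0.30 | 30% | 30% | 0 points |
| 0.30 | 0.50 | 43% | 30% | −13 points |
| 0.30 | 0.70 | 57% | 30% | −27 points |
| 0.50 | 0.30 | 37% | 50% | +13 points |

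The false difference can be zero or of either sign. Its size cannot be taken from the documents, but nothing in the stated analysis rules it out.

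**The case against.** The strongest reply has four parts.

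*The data may still be collected.* A reader might infer from the contradiction that help-seeking after self-harm will not be available. The documents do not show that. The interview questions come from an instrument that is not at hand, and the cross-reference to 10.3 points outside the article. The questions may cover both periods. Nor do the documents show which section is wrong; the slip could be in the abstract. What stands is that the declared and listed outcomes differ.

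*Old acts are probably not meant.* Because everyone has self-harmed in the year before entry and items (iii) and (iv) have no time limit, a reader might infer that acts from before randomisation will be counted. That is possible on the literal wording but is not the natural reading. The items stand under follow-up headings, directly after one limited to six months, and baseline self-harm is collected separately. What stands is that the limit should be stated.

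*Conditioning is partly inherent, and denominators are often left to an analysis plan.* Contemplation-to-act time cannot exist without an act, and the analysis section names neither variable. It does, however, commit other outcomes as a class to between-arm comparison on available data, and its regression and non-parametric options do not remove the selection. It is true that selection arises mainly if the JCP changes who self-harms. If it does not, the subgroups are comparable in expectation. But the trial is sized on the premise that it does.

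*Imprecision outweighs bias.* With 22 v 7 people and 30% seeking help in each arm (assumed), the standard error of the difference is √(0.21/22 + 0.21/7), about 20 points. A reader might want a definite figure for the bias; the documents support none. The small numbers are a further reason not to test.

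**Conclusion.** The point holds on both counts. The before/after contradiction is plain on the page and rests on no assumption. The selection problem follows from the definition of the two outcomes together with the plan's own 36% and 12%. About 22 v 7 of 60 per arm would have an act, only differences of about 1.2 to 1.3 SD would be detectable at 80% power, and a between-arm test would not be a randomised comparison. The counts assume that the predicted rates occur and that every interview is completed. If the two arms self-harm at the same rate, the subgroups could be closer in size and in kind.

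The reach is limited. These are two secondary outcomes in a trial that its authors describe as exploratory and not definitive. The primary analysis and the sample size are not affected.

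**What to change.** 1. Make the abstract and Follow-up assessments (iv) name the same help-seeking construct, or record help-seeking before and after the act as two separate items. The sponsor should decide which was intended; the article does not tell.
2. State in items (iii) and (iv) that the index act must fall between randomisation and the 6-month interview, and that the items do not apply to participants without such an act.
3. Report contemplation-to-act time and help-seeking among those with an act descriptively by arm, with the number having an act as the denominator, and without a between-arm test read as a treatment effect.

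The cost is a few words, at most one added interview item, and no p-value for two secondary outcomes.

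Scoring everyone on whether they had an act with no help sought would restore a comparison of all randomised, but it is not recommended as the remedy because it would largely repeat the primary outcome. If 30% seek help in both arms (assumed), it gives 0.36 × 0.70 = 25% v 0.12 × 0.70 = 8% with no effect on help-seeking.

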### Self-harm follow-up data

Variables (i) and (ii) will be gathered from the following sources:

1. The follow-up interviews with participants at 6-months - participants will be asked to recall the approximate number of self-harm events occurring over the preceding six months. Variables (iii) and (iv) will be gathered using questions derived from Hawton et al [15].

2. Diaries: all participants will be supplied with a simple diary/calendar and will be asked to record all self-harm events on this (by simply circling the days of the month on which self-harm events occurred).

3. Electronic psychiatric case records.

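### The diary records days with self-harm, not events, so on the number of self-harm events it cannot be compared like for like with the interview

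*Protocol article*

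**What the plan says.** The Abstract (Methods/Design) names three primary outcomes: "any self-harm event, time to first episode of self-harm and number of self-harm events over the follow-up period". Follow-up assessments lists the count as variable (ii), "Number of self-harm episodes over the preceding 6-month period".

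Self-harm follow-up data then states: "Variables (i) and (ii) will be gathered from the following sources". The sources are the six-month interview, a diary and the electronic psychiatric case records. At interview, "participants will be asked to recall the approximate number of self-harm events occurring over the preceding six months". In the diary, participants are asked to "record all self-harm events on this (by simply circling the days of the month on which self-harm events occurred".

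The Statistical analysis plan section compares the sources on missing data, and on agreement by Lin's concordance correlation coefficient. It adds: "The primary outcome analysis will be repeated on all three outcome collection methods to determine if conclusions remain the same". It expects little disparity on any self-harm, and possibly more on the time of the first episode and the number of episodes.

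**The concern.** A circled day is a yes/no mark. It gives the number of days with self-harm, which equals the number of events only if nobody self-harms more than once in a day. The article does not make that assumption, does not define an episode as a self-harm day, and does not ask for a number per day.

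This matters more here than in most trials, because comparing collection methods is part of the purpose. The end of the Background gives finding the best methods of data collection as an aim, and the analysis section says the comparison will guide the choice of method and outcome for a definitive trial. If part of the disagreement on the count comes from the recording unit, the trial could judge the diary or recall to be unreliable when both were accurate. A count analysis repeated on the diary would also address a different outcome from the one on the interview.

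**Working it through.** **The plan's own figure.** The sample size rests on the proportion self-harming, 36% against 12%, with 80% power and two-sided 5%. With mean proportion 0.24 and difference 0.24:

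- Uncorrected n per arm = [1.96 × √(2 × 0.24 × 0.76) + 0.8416 × √(0.36 × 0.64 + 0.12 × 0.88)]² / 0.24² = (1.184 + 0.488)² / 0.0576 ≈ 48.5, so 49.
- With continuity correction: (48.5 / 4) × [1 + √(1 + 4 / (48.5 × 0.24))]² ≈ 56.5, so 57 per arm and 114 in total.

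The stated 114 is reproduced. It does not involve the count, so this point leaves it unchanged.

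**Units of the three sources.** Interview: events. Diary: days. Electronic records: episodes as recorded, with no counting rule given. No section converts one unit to another.

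**Share of events captured.** If the mean number of events per self-harm day is 1 + μ and every self-harm day is circled, the diary captures 1 / (1 + μ) of events.

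**Effect on Lin's coefficient, with no reporting error.** Let a person's days D have mean m and variance V, and let events be E = D + Poisson(μD). Then:

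- mean of E = (1 + μ)m
- Cov(D, E) = (1 + μ)V
- Var(E) = (1 + μ)²V + μm
- CCC = 2(1 + μ)V / [V + (1 + μ)²V + μm + μ²m²]

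The article gives none of m, V or μ, so all three are assumed. With negative binomial days, mean 5 and shape 0.5, V = 5 + 25 / 0.5 = 55.

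| Events per self-harm day (assumed) | Diary captures | CCC by formula, mean 5 | CCC simulated, mean 5 / mean 15 | CCC simulated, events per day varying between people, mean 5 / mean 15 |
|---|---|---|---|---|
| 1.0 | 100% | 1.00 | 1.00 / 1.00 | 1.00 / 1.00 |
| 1.5 | 67% | 165 / 187.5 = 0.88 | 0.88 / 0.885 | 0.79 / 0.795 |
| 2.0 | 50% | 220 / 305 = 0.72 | 0.72 / 0.72 | 0.57 / 0.57 |
| 3.0 | 33% | 330 / 660 = 0.50 | 0.50 / 0.50 | 0.34 / 0.33 |

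A second simulation set the proportion with no self-harm days at 0.64 (matching the 36% expected under usual treatment), with shape 0.3 and samples of 120. It gave about 0.87, 0.73 and 0.52 to 0.53 for 1.5, 2 and 3 events per day. The result depends little on the assumed distribution of days and strongly on events per day.

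**Can it be untangled later?** No. An interview total twice the diary total fits two events per circled day with perfect reporting. It fits equally well one event per day with recall doubling the true number. The calendar cannot tell these apart.

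**The case against.** The strongest reply is that the plan foresees more disparity on the number of episodes and undertakes to look into differing conclusions, and that learning which source suits which outcome is what an exploratory trial is for. The expectation is there, but the inquiry could not succeed on this point, because the within-day number was never recorded.

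It is also fair that the article does not say outright that Lin's coefficient, or the repeated primary analysis, is applied to the count. That sentence speaks of one primary outcome analysis, and Sample size (Assumptions) picks the proportion self-harming for the power calculation, partly for its consistency across methods. The count reading is an inference: the Abstract makes the count a primary outcome, the diary is a listed source for it, and Lin's coefficient is a measure for quantitative data. The point is therefore conditional on the sources being compared on the count.

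Three stronger readings are tempting but not supported:

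- A reader might infer that the count has no suitable planned analysis. The sentence on other outcomes also allows regression modelling, and the exact model may stand in an analysis plan that is not shown.
- A reader might infer that frequent self-harmers lose the largest share of events. With a common mean of events per day, the expected proportional loss is the same for everyone; only the absolute shortfall grows.
- A reader might infer that the diary is unsound for self-harm generally. It serves any self-harm, and time to first episode to the day, without difficulty.

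**Conclusion.** The point holds as a mismatch of units. The diary is named as a source for the number of self-harm episodes but can give only the number of self-harm days, and nothing in the article reconciles the two. If the sources are compared on the count, some disagreement is built in unless no participant self-harms twice in one day.

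The documents do not allow its size to be stated. It ranges from nothing, at one event per self-harm day, to a diary that captures a third of events with concordance of about 0.5 at three per day, or about 0.33 if the rate varies between people. These figures assume perfect reporting in both sources and rest on assumed rates. The other two primary outcomes and the sample size are untouched.

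**What to change.** Ask participants to write the number of episodes in each circled day, and state in the analysis section that the diary count is the sum of those numbers. This is one added line in the diary instruction and a sentence in the plan. The downside is slightly more effort on a task that was kept deliberately simple.

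If that is judged too burdensome, describe the diary as measuring self-harm days, and compare it on the count only with sources that can also be expressed as days. This costs more: the interview would need an added question on the number of days, and the records could be used only where entries can be assigned to days.

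Either way, the plan should say to which variables Lin's coefficient and the repeated analysis apply, and in which unit.

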### Randomisation procedure and methods to minimise bias

Participants will be randomised using the method of minimisation with a random component stratified by alcohol misuse [as measured by the Alcohol Use Disorders Identification Test (AUDIT) [13]] and depression [as measured by the Hospital Anxiety and Depression Scale (HADS) [14]]. The randomisation will be managed by the Clinical Trials Unit (CTU) at the Institute of Psychiatry. Confirmation of eligibility, consent, and baseline data will be obtained prior to randomisation. Bias in the recruitment and randomisation process will be avoided by having randomisation done centrally by the CTU, and hence concealment maintained from the investigators, and by keeping a log of all service users randomised and including them all in the analysis. The research worker collecting outcome data will be blinded to the allocation. Some outcome data will be obtained from electronic patient records, even for participants lost to follow-up interview. This will include any episodes of self harm, hospital admissions and service use recorded in the electronic records. Bias in the collection of outcome data will also be minimised by the use of standardised objective assessments and by blinding the researchers as far as possible to service user allocation. There will be specific instructions to participants and clinical teams not to disclose the treatment details of any study participant. Every effort will be made to maximise the single blindness of research workers, whose 'best guesses' of treatment arm status will be assessed after the final assessment in order to test whether their blindness was successfully maintained.

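### The diary as described marks only days with self-harm, so it cannot show partial non-completion, and the planned comparison of missing data will tend to understate the diary's share

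*Protocol article*

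**What the plan says.** Under Self-harm follow-up data, the article introduces three sources for time to first self-harm and number of episodes: "Variables (i) and (ii) will be gathered from the following sources". They are the 6-month interview, a diary or calendar, and electronic psychiatric case records. The diary is filled in "by simply circling the days of the month on which self-harm events occurred". No entry is described for a day or week without self-harm, or for the last day on which the diary was used. At interview, "participants will be asked to recall the approximate number of self-harm events occurring over the preceding six months".

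The Statistical analysis plan section expects that the three methods "are likely to differ on the amount of missing data", and continues: "We will compare proportions of missing data using chi-square tests and agreement between data collection methods using Lin's Concordance Correlation Coefficient". It adds: "The primary outcome analysis will be repeated on all three outcome collection methods to determine if conclusions remain the same". Analysis is of available data, and any difference in conclusions between methods is to be investigated. A stated purpose of the exercise is to choose collection methods and an outcome measure for a definitive trial.

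The section on randomisation and minimising bias adds: "Some outcome data will be obtained from electronic patient records, even for participants lost to follow-up interview".

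**The concern.** A diary with only positive entries does not separate two different states: the participant did not self-harm, or the participant stopped recording. Someone who keeps it for six weeks, stops, and hands it in at month 6 returns the same page as someone who stopped self-harming at week six.

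Two parts of the plan depend on telling these apart. The first is the comparison of missing data between sources. For the diary, only non-return or evident non-use is visible. If half the participants stopped mid-way and all returned their diaries, the diary could show 0% missing. The second is the repeat of the primary analysis on diary data. If blanks are taken at face value, abandonment lowers the observed risk, delays or removes first events, and lowers counts. If one arm keeps the diary longer than the other, the comparison between arms is distorted.

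An analysis plan written later can set a coding rule for blanks, but it cannot recover information that the form did not collect.

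**Working it through.** **The plan's own figure.** Inputs from the Sample size section: 36% (TAU) and 12% (JCP), 80% power, two-sided 5%, 1:1. The mean proportion is 0.24 and the difference 0.24.

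- Uncorrected: n = [1.96·√(2·0.24·0.76) + 0.8416·√(0.36·0.64 + 0.12·0.88)]² / 0.24² = (1.1838 + 0.4879)² / 0.0576 = 48.5, so 49 per arm.
- Continuity-corrected: (48.5/4)·[1 + √(1 + 4/(48.5·0.24))]² = 56.5, so 57 per arm, 114 in total.

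This reproduces the stated 114, and 114/0.95 = 120. Neither figure is in dispute. The allowance from 114 to 120 is tied to administrative data, not to the diary.

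**Size of the diary problem.** The document gives no abandonment rate or coding rule, so the following are assumptions: constant hazard; a fraction *a* of participants abandon the diary at a time uniform over the six months and unrelated to self-harm; all diaries are returned; blanks are read as event-free.

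1. True risk r and hazard h = −ln(1 − r). TAU: h = −ln(0.64) = 0.446. JCP: h = −ln(0.88) = 0.128.
2. Risk of an event before a uniform abandonment time: q = 1 − (1 − e^−h)/h. TAU: 1 − 0.36/0.446 = 0.193. JCP: 1 − 0.12/0.128 = 0.061 (with h unrounded).
3. Observed risk = (1 − a)·r + a·q.

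| | a = 0 | a = 0.2 | a = 0.5 |
|---|---|---|---|
| True 36% | 36% | 0.288 + 0.0387 = 32.7% | 0.180 + 0.0967 = 27.7% |
| True 12% | 12% | 0.096 + 0.0123 = 10.8% | 0.060 + 0.0306 = 9.1% |

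**Comparison between arms.**

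- Equal abandonment of 50%: risk ratio 0.0906/0.2767 = 0.328, against a true 0.333. The ratio hardly moves, although both risks and their difference shrink.
- Unequal abandonment (50% in one arm, 20% in the other), true risks 36% and 12%: 0.0906/0.3267 = 0.28 if JCP participants abandon more; 0.1083/0.2767 = 0.39 if TAU participants do.
- Unequal abandonment, no true effect (36% in both arms): 32.7% − 27.7% = 5.0 points. At 60 per arm the standard error is √[(0.327·0.673 + 0.277·0.723)/60] = 0.084, so this is 0.6 standard errors. The two-sided rejection rate is about 9% instead of 5%.

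**Power of a diary-only analysis.** Let m be the share of participants with events whose diary shows none. In the model above, m for TAU is 1 − 0.327/0.36 = 9% at a = 0.2 and 1 − 0.277/0.36 = 23% at a = 0.5. With 60 per arm and no continuity correction, power is 0.88 at m = 0, 0.83 at 10%, 0.77 at 20% and 0.70 at 30%, with m equal in both arms.

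**Check on a tempting remedy.** Suppose diaries that stop early without an event are coded missing for any self-harm, while those that stop after an event are kept. The risk among analysed diaries is [(1 − a)·r + a·q] / [(1 − a) + a·q].

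- True 36%, a = 0.2: 0.3267/0.8387 = 39.0%.
- True 36%, a = 0.5: 0.2767/0.5967 = 46.4%.

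With no true effect, 50% against 20% abandonment now gives a gap of 7.4 points, larger than the 5.0 points it was meant to remove. With true risks of 36% and 12%, the risk ratio becomes 0.1708/0.3895 = 0.44 or 0.1333/0.4637 = 0.29. The rule selects on the outcome and should not be used.

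**The case against.** The strongest reply is that the diary is one of three sources. The interview covers the same six months, case records reach participants lost to interview, agreement between methods is measured, and discrepancies are to be investigated. A diary abandoned at week six would often show fewer events than the same person reports at interview. The Discussion also promises to examine selective dropout by arm. All this stands, and it confines the problem to diary-based results and the source comparison. It does not remove the problem. A concordance coefficient shows that sources disagree. It does not show whether a blank diary beside a positive interview reflects abandonment or inaccurate recall, and the interview asks only for an approximate number.

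A second reply is that the form itself is not shown and that coding rules belong in a fuller protocol or SAP. This stands as a limit on certainty: the finding rests on the diary as the article describes it. If the actual form already has a completion mark, the point falls away.

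A third reply is that every abandonment rate above is assumed. That is correct. Unequal diary-keeping is possible, since only JCP participants have planning meetings with a research worker, but nothing in the article shows that it would occur or in which direction.

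**Conclusion.** The point holds in a limited form. As described, the diary cannot separate no self-harm from no recording within a returned diary. The planned comparison of missing data therefore cannot detect partial diary non-completion and will tend to understate it, and the diary-based repeat of the primary analysis could read abandonment as absence of self-harm.

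Under the stated assumptions, a true 36% would be observed as 32.7% (20% abandon) or 27.7% (50% abandon). Equal abandonment leaves the risk ratio almost unchanged and mainly costs power. Bias between arms needs unequal abandonment: a 30-point gap between arms yields about 5 points, against a planned difference of 24.

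A reader might infer that the trial analyses non-completion as absence of self-harm, or that its choice of collection method will come out wrong. The document supports neither. It states no coding rule for blank stretches, it treats missing diary data as something to be measured, and the choice of method also draws on agreement statistics and a review of discrepancies.

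**What to change.** 1. Add one tick per week to the calendar, confirming that the diary was kept and there was no self-harm that week. Treat a week with neither a tick nor a circle as missing.
2. Use completed weeks as the diary's completeness measure when missing data are compared between sources.
3. For the diary source, censor time to first self-harm at the last completed week. Estimate the 6-month risk of any self-harm from that censored analysis, for example by Kaplan–Meier, and state the assumption that stopping the diary is unrelated to self-harm.
4. Do not code only event-free early stoppers as missing.

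The cost is a small change to a printed form and a short coding rule. Participants carry slightly more burden, and the diary's stated missing rate will be higher because it then includes partial non-completion.
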